#### 8.4.2 UNANTICIPATED PROBLEMS REPORTING

Incidents or events that meet the OHRP criteria for unanticipated problems require the creation and completion of an unanticipated problem report form. OHRP recommends that investigators include the following information when reporting an adverse event, or any other incident, experience, or outcome as an unanticipated problem to the IRB:

- Appropriate identifying information for the research protocol, such as the title, investigator’s name, and the IRB project number;
- A detailed description of the adverse event, incident, experience, or outcome;
- An explanation of the basis for determining that the adverse event, incident, experience, or outcome represents an unanticipated problem;
- A description of any changes to the protocol or other corrective actions that have been taken or are proposed in response to the unanticipated problem.

To satisfy the requirement for prompt reporting, unanticipated problems will be reported using the following timeline:

- Unanticipated problems that are serious adverse events will be reported to the IRB, IMC, and NCCIH within 7 days of the investigator becoming aware of the event.
- Any other unanticipated problem will be reported to the IRB, IMC, and NCCIH within 14 days of the investigator becoming aware of the problem.

All unanticipated problems should be reported to appropriate institutional officials (as required by an institution’s written reporting procedures), the supporting agency head (or designee), and OHRP within one month of the IRB’s receipt of the report of the problem from the investigator.

---

#### 8.4.3 REPORTING UNANTICIPATED PROBLEMS TO PARTICIPANTS

N/A

## 9 STATISTICAL CONSIDERATIONS

### 9.1 STATISTICAL HYPOTHESES

We hypothesize that:

- Primary Endpoint(s):
  - Participants in the RESILIENCE program arm will demonstrate greater improvements in resilience assets and resources as measured by CD-RISC scores at 3-months (post-treatment) relative to those in the attention control arm (physical activity program).
- Secondary Endpoint(s):
  - Participants in the RESILIENCE arm will demonstrate better maintenance of CD-RISC scores at 9- and 15-months (follow-up) than those in the attention control arm (physical activity).
  - Participants in the RESILIENCE arm will demonstrate greater improvements in well-being (general health questionnaire) at 3-, 9-, and 15-months compared with those in the attention control arm.
  - The organizational support and resources of centers in both groups will improve significantly as assessed using the NIOSH worker well-being questionnaire (WellBQ).

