| Objectives*:                                                 | 
The primary objective will test the efficacy of a resilience and stress management program compared to a physical activity program on change in resilience resources and assets (baseline to 3 months). A secondary objective will be to examine change in resilience over a maintenance period (3 months to 9 and 15 months). An additional secondary objective will be to examine change in organizational support and resources, absenteeism, and staff turnover between programs in the two groups.
                                                                                                                                                                                                                                                                                                                                                                                                                                                                                                                                                                                                                                                                                                                                                                                                                                                                      |

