| Change in Resilience from 9 to 15 months       | Resilience of ECE staff will be assessed using the Connor-Davidson Resilience Scale (CD-RISC). ECE staff will fill out through an online survey. The CD-RISC is a 25-item scale. Scores range from 0-100 with higher scores reflecting greater resilience.                                                                            | The CD-RISC is the most commonly used assessment of resilience in research.  Data are used to calculate an overall resilience score. The overall score has demonstrated internal consistency (Cronbach's alpha = (0.89), been shown to be negatively correlated with stress ( $r=-0.76$ , $p<0.001$ ),  and sensitive to change in several of our team's previous pilot studies.  |
| Change in Well-Being from Baseline to 3 months | Global assessment of well-being will be measured through the General Health Questionnaire. This is a 30-item survey captures a broad spectrum of psychological distress encompassing emotional, cognitive, and social aspects of mental health. Scores range from 0-90, with higher scores indicating greater psychological distress. | The Global Health Questionnaire was recommended in a review of resilience interventions for its ability to capture a global assessment of mental health, including anxiety, difficulty coping, depression, feelings of incompetence, and social dysfunction. Cronbach's alpha= 0.92                                                                                                                                           |

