| Change in Organizational Support and Resources from Baseline to 3 months | Organizational support and resources will be assessed using the NIOSH worker well-being questionnaire (WellBQ). Specifically, eight Likert-type items from the supportive work culture and health culture at work sections of the survey will be averaged to create this outcome. Items are rated on 1 to 4 scale from strongly disagree to strongly agree, with the final outcome being an average score ranging from 1.00 to 4.00.                                                                                        | The NIOSH WellBQ is a well researched and strongly developed assessment of worker well-being across multiple domains.                                                                                                                                                                                                                                                   |
| Absenteeism from Baseline to 3 months                                    | Staff absenteeism will be assessed by asking staff how often they "missed a full day of work" and "missed 1/2 day of work" in the past 4 weeks. Directors will also be asked "On average, how many days per month do staff miss a full day of work when scheduled to be at your center?". Items will be combined to estimate "Days per month staff missed work" at a center.                                                                                                                                                | Common questions used to assess missed work and impact on organizational function.                                                                                                                                                                                                                                                                                      |

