## 4 STUDY DESIGN

### 4.1 OVERALL DESIGN

This study will use a cluster-randomized control trial to evaluate change in resilience assets and resources for early childhood education (ECE) center staff. To evaluate the impact, measurements will be collected at four time points, baseline, post intervention (3 months), and maintenance (9 months and 15 months). All data collection will be completed remotely, using self-report surveys and phone/audio conferencing interviews. ECE centers will be randomized to receive either the resilience intervention or a physical activity (attention matched control) intervention.

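### The organizational-support hypothesis is worded as improvement within both arms, whereas the objective and planned model compare the arms and there is no untreated arm to support a within-arm claim

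*Protocol*

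**What the plan says.** Section 9.1 lists one primary and three secondary hypotheses. The primary and the first two secondary hypotheses compare the Resilience arm with the attention control. The third secondary hypothesis does not: "The organizational support and resources of centers in both groups will improve significantly". It names no comparator and no time point.

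Elsewhere the protocol treats the same outcome differently:

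- The synopsis gives the objective as to "examine change in organizational support and resources, absenteeism, and staff turnover between programs in the two groups".
- The endpoint table in section 3 lists "Change in Organizational Support and Resources from Baseline to 3 months". The outcome is the mean of eight WellBQ items, "with the final outcome being an average score ranging from 1.00 to 4.00". The table does not say whether arms are compared.
- Section 9.4.3 refers secondary endpoints to section 9.4.2. That section tests change between the two arms in a mixed model with time, arm and their interaction.
- Section 4.1 describes the arms: "ECE centers will be randomized to receive either the resilience intervention or a physical activity (attention matched control) intervention". Sections 4.2 and 6.1.1 confirm that the comparator is itself a full program.

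A smaller mismatch concerns the General Health Questionnaire. Section 9.1 hypothesizes "greater improvements in well-being (general health questionnaire) at 3-, 9-, and 15-months compared with those in the attention control arm", while the endpoint table lists only "Change in Well-Being from Baseline to 3 months".

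**The concern.** As worded, the hypothesis is met when each arm shows a significant before-after change. Randomization carries no information about that event, because neither arm shows what would have happened without a program. A before-after change mixes any program effect with whatever else moves the score over three months, such as repeat completion of the survey or selective loss of less supported staff.

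The wording can also give the opposite answer to the planned test. If both programs helped equally, the hypothesis would be confirmed and the arm-by-time contrast would be null. If neither helped but scores drifted upward, the result would look the same. A report could then state that both programs improve organizational support, citing a prespecified hypothesis, without a randomized comparison behind that statement.

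**Working it through.** **The plan's own figure.** There is none for this hypothesis. The power statement in section 9.2 (90%) is for the between-arm CD-RISC difference. With 40 centers per arm, 8 workers per center, ICC 0.10 and effect 0.35, equal clusters give a design effect of 1 + 7 × 0.10 = 1.7 and power 0.924 (normal approximation). Assuming a cluster-size coefficient of variation of 0.5, the design effect is 1 + (1.25 × 8 − 1) × 0.10 = 1.9 and power is 0.895, matching the stated 90%. The point below does not depend on this figure.

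**Inputs.** From section 9.2: 40 × 8 = 320 workers per arm, and ICC about 0.10, hence design effect 1.7. Assumed, because the protocol gives no WellBQ SD, correlation, ICC or trend:

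- the CD-RISC planning ICC applies to WellBQ change;
- the change SD equals the score SD (baseline to 3-month correlation 0.5);
- the arms are independent;
- alpha is two-sided 0.05;
- the program effect is zero;
- both arms share the same drift *d*, in score SDs.

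**Step 1, one arm.** SE of the mean change = √(1.7/320) = 0.0729 SD. The chance of a significant improvement is Φ(d/0.0729 − 1.96).

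- d = 0.15: Φ(2.06 − 1.96) = 0.54
- d = 0.20: Φ(2.74 − 1.96) = 0.78

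**Step 2, both arms.** The hypothesis needs both, so the per-arm chance is squared.

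- d = 0.15: 0.54² = 0.29
- d = 0.20: 0.78² = 0.61
- d = 0: 0.025² = 0.0006

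With the 15% loss that section 9.2 considers, 272 workers per arm remain, the SE is √(1.7/272) = 0.079, and the joint chances are about 0.23 and 0.51.

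**Step 3, simulation.** Center-mean change scores were simulated 20,000 times per setting, with the same drift in both arms and no program effect. Significance in each arm was judged by a t-test on centers. The main column uses 40 centers per arm, ICC of change 0.10 and correlation 0.5. The ranges cover ICC 0.03 to 0.13 and correlation 0.3 to 0.7.

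| Common drift (SD) | Both arms improve, main setting | Range, 40 centers per arm | Range, 34 centers per arm | Between-arm test |
|---|---|---|---|---|
| 0 | about 0.001 | 0.001 or less | 0.001 or less | about 0.05 |
| 0.10 | 0.07 | 0.035–0.28 | 0.03–0.22 | about 0.05 |
| 0.20 | 0.58 | 0.33–0.97 | 0.25–0.93 | about 0.05 |
| 0.30 | 0.96 | 0.80–1.00 | 0.69–1.00 | about 0.05 |

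The simulated 0.58 at 0.20 SD agrees with the 0.61 from the formula. The between-arm test holds its level because a shared drift cancels. The weakness is therefore confounding with time, not multiplicity.

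**The case against.** The strongest reply is that the remedy is mostly in place. The model in section 9.4.2 applies to secondary outcomes and supplies the randomized contrast, so a reader who infers that the trial will have no randomized evidence on organizational support goes too far. It would also be wrong to say that the model cannot address the hypothesis as worded, because its contrasts can estimate within-arm change. Both replies stand. They place the fault in the hypothesis statement, not in the analysis.

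A reader might take the per-arm chances of 54% and 78% as the rate of false confirmation. They are not, because the hypothesis requires both arms; the joint figures are 29% and 61%. All of these need a drift that the protocol neither reports nor predicts, and at 0.10 SD the chance is only 0.07 in the main setting.

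Two sources of drift are also weaker than they first appear. Section 5.5 spreads enrolment over about 2 years, so a seasonal effect would partly average out. The likelihood analysis keeps the baseline data of staff who leave, which limits selective loss to the extent that data are missing at random. Repeat-survey effects are not addressed by either.

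Finally, expecting both programs to help is compatible with comparing them; section 2.3.2 anticipates benefit in either program. Section 9.1 also does not say that improvement will be credited to the programs, so misattribution is a risk and not a stated intention. That is fair, but a prespecified hypothesis should be one the design can test, and it should match its own objective.

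**Conclusion.** The point holds as an inconsistency in one secondary hypothesis. Section 9.1 asks a within-arm question, the synopsis asks a between-program one, and sections 9.4.2 and 9.4.3 plan to answer the latter. Because neither arm is untreated, the within-arm version cannot show that a program caused the change; this follows from the design and needs no numbers.

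The size is conditional. Confirmation without any program effect becomes likely only with a shared drift of roughly 0.2 SD or more, and the exact chance rests on the assumed correlation, ICC and arm independence listed in the working. The primary endpoint, its model and its power are untouched. The General Health Questionnaire mismatch is a separate, minor matter of endpoint timing and adds no weight to the main point.

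**What to change.** In section 9.1, restate the organizational-support hypothesis as a between-arm difference in WellBQ change from baseline to 3 months, tested by the time-by-arm contrast already planned. Report the change within each arm with its confidence interval as descriptive only. If the investigators expect similar improvement in both programs, say so and state that this design cannot attribute it to them.

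Separately, make section 9.1 and the endpoint table in section 3 agree on the General Health Questionnaire time points, so that the status of the 9- and 15-month results is clear.

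The cost is wording: no new data, sample size or model. The sponsor gives up a confirmatory claim of improvement in both arms, which the design could not support.

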### 9.2 SAMPLE SIZE DETERMINATION

The study is powered to detect a between group difference (Resilience group vs attention control) of overall resilience assets and resources as assessed with the CD-RISC (primary outcome). An effect size of at least 0.35 is expected, representing a clinical meaningful difference and a conservative estimate based off the SMART resilience program's well-documented efficacy to facilitate change across several mental health related outcomes (with effect sizes ranging from 0.3 to 1.1). Based on previous work we anticipate that, on average, about 8 workers will participate at each childcare center. Since this is a cluster randomized design, we assume that there will be an inherent ICC within centers. The ICCs observed in our previous work assessing childcare worker health outcomes ranged from 0.00 to 0.13.

*Statistical power table* describes the power for a range of ICCs, number of centers per arm, and effect sizes. Given these assumptions, a sample size of 80 centers (40 per arm), with an

| Statistical Power |             |      |      |      |      |
|-------------------|-------------|------|------|------|------|
| Centers per arm   | Effect Size | ICC  |      |      |      |
|                   |             | 0.00 | 0.03 | 0.10 | 0.13 |
| 30                | 0.30        | 0.91 | 0.84 | 0.67 | 0.60 |
| 30                | 0.35        | 0.97 | 0.93 | 0.80 | 0.73 |
| 30                | 0.40        | 0.99 | 0.98 | 0.89 | 0.84 |
| 35                | 0.30        | 0.94 | 0.89 | 0.73 | 0.67 |
| 35                | 0.35        | 0.99 | 0.96 | 0.85 | 0.80 |
| 35                | 0.40        | 1.00 | 0.99 | 0.93 | 0.89 |
| 40                | 0.30        | 0.97 | 0.92 | 0.79 | 0.73 |
| 40                | 0.35        | 0.99 | 0.98 | 0.90 | 0.85 |
| 40                | 0.40        | 1.00 | 0.99 | 0.96 | 0.93 |

average of 8 workers per center, and an ICC ~0.10 would allow us to detect an effect size of 0.35 with 90% power at  $\alpha=0.05$  level of significance. Even with a 15% loss to follow-up at 3 months (e.g., 12 centers or 96 workers), which is higher attrition than we expect based on our previous childcare-based trials, a completer's only analysis will still provide 84% power. An important secondary aim is to compare the maintenance of resilience interventions from 3 months to 15 months. Anticipating higher loss to follow-up at 15 months and assuming a minimal detectable effect size of at least 0.35, we retain 82% power with an ICC = 0.10 with 20% attrition (e.g., 16 centers or 128 workers). Missing data will be fully recovered as

discussed in section 9.4.2 (below), which will remove or minimize (if present) confounding effects of missingness on our statistical power.

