#### 4.2 SCIENTIFIC RATIONALE FOR STUDY DESIGN

Recently, there has been a call for resilience researchers to move beyond single-arm and wait-list control study designs to those that are randomized, controlled, and include matched attention comparison groups. Although there is no current consensus on what type of attention control is best for resilience research, the use of physical health promotion interventions (e.g., physical activity, nutrition) have been shown to be feasible and acceptable. Therefore, we have chosen our teams' physical activity promotion program used in previous and ongoing (R01 DK128174) childcare-based worksite wellness trials. Offering an alternative health promotion program will be perceived as a positive alternative to a waitlist for workers randomized to the control group. Additionally, this affords an opportunity to assess the efficacy of the Resilience program compared to a program that has the potential to be a comparable, or alternative, therapy for stress and anxiety reduction for ECE workers. In the attention control group, participants will be provided a low-cost activity tracker (e.g., Amazfit Band). Similar to the Resilience program components will be delivered in four phases over 3-months with implementation supported by trained research staff. Timeline and logistical components will match the Resilience program.

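### Section 9.2 says missing data will be fully recovered, but 90% power holds only with complete 3-month follow-up; at 15% loss it is about 84-88%

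*Protocol*

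**What the plan says.** Section 9.2 (Sample Size Determination) plans "a sample size of 80 centers (40 per arm), with an" average of 8 workers each, and states that "an ICC ~0.10 would allow us to detect an effect size of 0.35 with 90% power" at a 0.05 "level of significance". For a 15% loss at 3 months, given as 12 centers or 96 workers and described as more than the team expects, it adds that "a completer's only analysis will still provide 84% power". For 20% loss at 15 months it gives 82%.

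The section then closes with "Missing data will be fully recovered as" described in Section 9.4.2, and says this will remove or minimize the effect of missingness on power.

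Section 9.4.2 describes a mixed model fitted by maximum likelihood to all observed data under missing at random. If missingness exceeds 5%, it adds multiple imputation with auxiliary variables. Section 9.3 makes the analysis of all randomized participants primary and the completers analysis additional.

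**The concern.** The 84% is tied to a completers-only analysis, and the next step in the text is full recovery of missing data. Read in order, this tells the reader that 84% belongs to a secondary analysis and that the primary intention-to-treat analysis keeps the 90%. Neither method in Section 9.4.2 can do that. Likelihood and imputation under missing at random use the observed data efficiently and guard against some bias, but a 3-month score that was never collected is replaced only as far as other observed values predict it.

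At stake is how the trial's sensitivity is understood. Anyone who later judges the width of the interval, or a non-significant result, against 90% power would be using a figure that applies only if every worker is measured at 3 months.

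**Working it through.** **Inputs from Section 9.2.** 40 centers per arm; 8 workers per center; ICC 0.10; effect size d = 0.35; alpha 0.05; 15% loss at 3 months (12 centers or 96 workers); 20% loss at 15 months (16 centers or 128 workers). Sidedness is not stated; two-sided is assumed.

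**Formula.** For k centers per arm and m workers per center:

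- design effect = [1 + (m − 1) × ICC] / (1 − ICC)
- effective n per arm = k × m / design effect
- power = Φ(d × √(n/2) − 1.96)

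The division by (1 − ICC) means that d is in within-center SD units. The protocol does not name its SD, but this form reproduces all 36 cells of its power table within 0.005. The usual design effect, with d in total-SD units, gives 92.4% for the headline and misses some cells by up to 6 points.

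**Step 1: the protocol's own figures (d = 0.35).** With m = 8 the design effect is 1.7/0.9 = 1.889.

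| Case | k × m per arm | Effective n | Power | Protocol |
|---|---|---|---|---|
| Complete follow-up | 40 × 8 | 169.4 | 89.6% | 90% |
| 12 centers lost | 34 × 8 | 144.0 | 84.4% | 84% |
| 16 centers lost | 32 × 8 | 135.5 | 82.2% | 82% |

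All three figures reproduce.

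**Step 2: the same 15% lost as workers spread over all centers.** Now m = 6.8, the design effect is 1.58/0.9 = 1.756, and effective n = 272/1.756 = 154.9. Completers-only power is 86.9%. The protocol's 84% is therefore the whole-center version of its 15% scenario.

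**Step 3: what likelihood methods regain.** Let r be the correlation between the baseline and 3-month CD-RISC scores. The protocol does not give it; 0.5 to 0.7 is assumed. As an approximation, the variance of the estimated 3-month mean relative to no loss is (1/0.85) × (1 − 0.15 × r²):

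- r = 0.5: 1.1765 × 0.9625 = 1.132
- r = 0.7: 1.1765 × 0.9265 = 1.090

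Dividing the sample by this ratio gives:

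| r | Loss treated as centers | Power | Loss treated as workers | Power |
|---|---|---|---|---|
| 0.5 | 40/1.132 = 35.3 centers | 85.7% | 8/1.132 = 7.06 per center | 87.6% |
| 0.7 | 40/1.090 = 36.7 centers | 87.0% | 8/1.090 = 7.34 per center | 88.2% |

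The result is about 86-88%. With r = 0.9 it is still only 88.7-89.1%. The variance ratio returns to 1, and power to 89.6%, only when r = 1.

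**Step 4: the lower tabulated effect, d = 0.30.** Completers-only power is 78.8% with no loss (0.79 in the protocol's table), 72.1% with 12 centers lost and 75.2% with workers lost across centers.

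**Step 5: dependence on the SD convention.** In total-SD units at d = 0.35, completers-only power is 92.4% with no loss and 87.9-90.1% with 15% loss. The level moves; the drop does not disappear.

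**The case against.** The strongest reply is that the protocol hides nothing. It states 84% at 15% loss and 82% at 20% loss, both correct. It calls 15% more than it expects, and it says the methods will remove or minimize the effect of missingness; partial recovery is a fair meaning of minimize. If workers rather than centers are lost, likelihood methods leave power only about 2 points below 90%.

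Most of this stands. It limits the point to one claim and its implication for the primary analysis. It does not rescue the claim, because full recovery is stated without qualification and the softer clause comes after it.

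Three stronger readings are tempting, and the documents support none of them:

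- **That 15% is the planned attrition, so the trial's power is really 84%.** Section 9.2 presents 15% as a pessimistic scenario, and 84% applies to whole-center loss in an analysis that is not primary.
- **That power is 72% at the lower effect of 0.30.** That figure needs d = 0.30 and loss of 12 whole centers together. With no loss the table gives 0.79; with worker-level loss it is 75%.
- **That calling 0.35 conservative is an error.** Section 9.2 says "An effect size of at least 0.35 is expected, representing a clinical meaningful difference and a conservative estimate", citing prior work "with effect sizes ranging from 0.3 to 1.1". The value is not the lower end of that range, and Section 4.2 describes the comparator as "a program that has the potential to be a comparable, or alternative, therapy for stress and anxiety reduction". But 0.35 lies near the bottom, the range covers several outcomes, and the comparators behind it are not described. The label is a judgment, and the effect of an active control on it cannot be quantified from the protocol.

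**Conclusion.** The point holds as an incorrect statement about missing data, not as an arithmetic error. The 90% belongs to complete 3-month follow-up. In the protocol's 15% scenario, at d = 0.35 and ICC 0.10, power is 84-87% for completers and about 86-88% with likelihood methods. The shortfall from 89.6% is between roughly 1 and 5 points.

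This rests on a two-sided test, equal center sizes, the effect size in within-center SD units (the only convention tried that matches the table), and an assumed baseline to 3-month correlation of 0.5-0.7. The likelihood figures also assume missing at random.

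**What to change.** In Section 9.2:

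- Replace the sentence on full recovery with one saying that the Section 9.4.2 methods use all observed data and, under missing at random, partly recover the information lost.
- Label 90% as the power with complete 3-month follow-up.
- Give 84-88% as the power at 15% loss, depending on whether centers or workers are lost and on the analysis used, and state the correlation assumed.
- Name the SD by which the effect size is standardized, since the percentages depend on it.
- Optionally, show d = 0.30 with 15% loss (72-75% completers-only) beside the tabulated 79%.

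The cost is a few lines of text and a slightly less favorable power statement. Enrollment, design and analysis do not change, and the word conservative can stay.
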